### 2.5. Randomization and Blinding

A total of 48 participants will be randomly allocated in 2 groups, with 24 participants in each group. The sequence will be generated randomly by computer and the participants will be allocated to EG or CG.

Two members of the research team will perform the assessments and will be blinded to group and treatment assignments.

### 2.6. Study Flow

Figure 1 shows the flow chart of this RCT following the CONSORT guidelines [30,31].

Figure 2 shows the schedule of enrollment, interventions, and assessments based on the SPIRIT statement [29].

### 2.7. Outcome Variables

After randomization, sociodemographic, clinical, and outcome variables will be collected at baseline assessment (A_0_). PT interventions will be carried out in each group for 6 weeks. After group interventions, an intermediate assessment (A_1_) will be performed, and a follow-up assessment (A_2_) will be carried out 12 weeks from baseline (Table 1). The assessments will be carried out by 2 Pediatric Physiotherapists (PPT), members of the research team, after training and consensus meetings.

Primary outcomes are as follows:

Participation: measured with the Spanish version of the Children’s Assessment of Participation and Enjoyment—CAPE, which has good internal consistency, construct validity, convergent and discriminant [40]. This instrument measures participation in extracurricular leisure activities in children and adolescents with and without disabilities during the last 4 months. It includes 55 activities, and each activity is categorized by domains (Formal, Informal) and type (Recreational, Physical, Social, Skills-based and Self-Improvement). In addition, it also measures the diversity and intensity of participation, with whom they participate and where, and the enjoyment in performing the activity.

Gross motor function: measured with the Spanish version of Gross Motor Function Measure—GMFM-SP [41], which consists of 88 items to assess the gross motor function in 5 dimensions: lying and rolling (A), sitting (B), crawling and kneeling (C), standing (D) and walking, running and jumping (E). From each dimension, a score of 0 to 100% is obtained, where a greater percentage means a greater number of items achieved. For this study, dimensions D and E are established as the goal dimensions. The minimum clinically important difference in children and adolescents with levels II and III in GMFCS is 1.5% and 1.2%, respectively [42].

Secondary variables are as follows:

Gait speed: measured with the 10 m walk test—10 MWT [43] in meters/second, which allows quick and easy assessing of walking speed. It is a commonly used test, both in clinical settings and in research, and it is outstanding for a high degree of intra- and inter-observer reliability [44].

Gait endurance: assessed with the 6 min walk test—6 MWT [45] that measures the distance, in meters, that an individual is able to walk for 6 min. It stands out for being easily reproducible, highly standardized and sensitive to changes, and it is the most reliable scale for the assessment of gait endurance [44].

Static and dynamic balance: assessed with the Spanish version of Pediatric Balance Scale—PBS [46]. It consists of 14 items to be scored from 0 to 4, 0 being the inability to perform the task and 4, the ability to perform the task following the guidelines described in each item without difficulty. The result is obtained by adding the score, which can reach a maximum of 56 points. The minimum clinically important difference is an increase in score between 3.66 and 5.83 points [47].

Functional goals: goal-setting will follow SMART criteria, and a maximum of 3 functional goals will be identified and defined by each participant [48,49]. They will be rated with the Goal Attainment Scaling (GAS), a 6-point-scale for measuring significant and realistic functional goals, and demonstrated to be a feasible outcome measure [50].

The telecare program will be carried out by remote assistance with the Alcalá University online campus, through the BlackBoard Ultra™ digital platform (https://uah.blackboard.com/ultra/institution-page, accessed on 17 January 2024), with 6 online sessions, 1 per week. The sessions will consist of approximately 60 min of a family-centered EP, which includes AOT activities [51]. The inclusion of a telecare EP program aims to enhance family involvement, provide additional guidance, and reinforce therapeutic strategies in a home-based setting, complementing their standard PT routines.

Session 1: Concept and causes of CP, general program goals and guidelines.

Session 2: The family-centered model: discussing the importance of involving family in the development of goals and tasks included in the physical therapy intervention to translate the child and/or adolescent’s new learning to their natural environment and to promote collaboration with the treatment team’s guidelines. To offer opportunities to discover what they want to achieve, clarify what they need to achieve those goals, and recognize what they already know and what they can do. To define what they still need to learn and do to improve children’s functional activity and participation in their environment.

Sessions 3, 4 and 5: AOT activities through observation of actions performed by other individuals to facilitate the activation of the same neural structures involved in the execution of the observed actions. According to participants’ age and functional level, videos will be recorded with actions that are familiar to them and with activities that are related to walking (getting up from/sitting in a chair, walking down a corridor, etc.) in their natural environment.

Session 6: Program evaluation with different activities on participation, learning strategies and integration of AOT activities into daily life.

Figure 3 illustrates FIMAPACE telecare program.

#### 2.8.2. Control Group Intervention

Participants assigned to the CG will continue their regular PT intervention routines at their schools and centers for 6 weeks. In addition to that, they will also participate in the same family-centered EP as the EG. This ensures that all participants receive consistent educational support while maintaining their existing therapeutic interventions.

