## Abstract

**Background:** People with cerebral palsy (CP) present with limitations in gait and functionality, with a great impact on participation. Physiotherapy interventions based on goal-directed training (GDT), treadmill gait training (TGT), and action observation treatment (AOT) showed to be effective for improving functionality, gait and balance in children and adolescents with CP. On the other hand, since COVID-19 lockdown, telecare has an increased role in physiotherapy interventions. The aim of this randomized controlled trial (RTC) is to analyze the effectiveness of a multimodal intervention that combines face-to-face PT sessions of GDT and TGT and online PT sessions of a family-centered education program, which includes AOT activities and is effective to improve participation, gross motor function, gait and balance in children and adolescents with CP. **Methods:** A single-blinded RCT is proposed for 48 children and adolescents with CP (6–17 years old) who will be randomly allocated into two groups: the experimental group will receive six weeks of a multimodal PT intervention with 12 face-to-face sessions (GDT and TGT) and 6 online sessions of a family-centered telecare EP, which includes AOT activities. Participants in the control group will carry on with their regular PT treatment plus the EP as the experimental group. The outcome variables of participation (CAPE); gait speed and endurance (10 mm/6 mm); gross motor function (GMFM-88-SP); and dynamic and static balance (PBS) will be collected at baseline, after group interventions and 12 weeks from baseline and will be compared following standard principles for RCTs. **Conclusions**: The implementation of a multimodal PT intervention that combines face-to-face sessions of GDT and TGT and online sessions of a family-centered EP, which includes AOT activities, may be effective to improve participation, gross motor function, gait and balance in children and adolescents with CP. Trial registration: ClinicalTrials.gov with ID: NCT04778930.

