Therefore, the aim of this randomized controlled trial (RTC) is to analyze the effectiveness of a multimodal PT intervention that combines face-to-face sessions of GDT and TGT and online sessions of a family-centered EP, which includes AOT activities, to improve participation, gross motor function, gait and balance in children and adolescents with CP.

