Therefore, effective multimodal PT interventions that are personalized to align with individual functional goals and integrate active, meaningful task-specific training—enhanced by telecare—hold significant potential for improving motor abilities and promoting greater participation. By emphasizing task-oriented training in real-life contexts, these interventions facilitate the transfer of improved gait functionality into everyday settings. Encouraging participants and their families to continue practicing therapeutic activities at home and within their communities reinforces motor learning and fosters long-term functional gains [12,15,35]. Furthermore, the systematic review conducted by Lucas et al. [14] underscores the urgent need for high-quality intervention trials to refine and expand evidence-based strategies aimed at enhancing gross motor function in children and adolescents with cerebral palsy. The findings emphasize the necessity of developing and implementing interventions that are not only effective but also adaptable to diverse environments, ensuring broader accessibility and applicability in real-world settings.

The findings of this study will help to highlight the importance of family/child/adolescent-centered interventions tailored to their specific needs. Incorporating intervention sessions within the child’s or adolescent’s natural environment—whether at home or in the community—enhances the relevance and applicability of therapy, promoting greater engagement and functional improvements. This approach is expected to facilitate meaningful progress in essential motor skills, fostering independence and improving overall quality of life. Furthermore, by integrating therapy into daily routines, this model encourages sustained participation and long-term benefits beyond the structured intervention period [52].

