## 4. Conclusions

The implementation of a multimodal PT intervention that combines face-to-face sessions of GDT and TGT and online sessions of a telecare family-centered EP, which includes AOT activities, may be effective to improve participation, gross motor function, gait and balance in children and adolescents with CP.

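### Both arms get the same education programme with action observation, so the trial tests the face-to-face programme and not the whole package named in the aim and conclusion

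*Protocol article*

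**What the plan says.** **Aim.** The Introduction states the aim as "the effectiveness of a multimodal PT intervention that combines face-to-face sessions of GDT and TGT and online sessions of a family-centered EP", with AOT as part of that programme. The Abstract gives the same aim.

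**Experimental group (EG).** The Abstract gives it "12 face-to-face sessions (GDT and TGT) and 6 online sessions of a family-centered telecare EP, which includes AOT activities", over six weeks. Section 2.8.1 places AOT inside the EP, in online sessions 3 to 5.

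**Control group (CG).** Section 2.8.2 says that controls "will continue their regular PT intervention routines at their schools and centers for 6 weeks" and that "they will also participate in the same family-centered EP as the EG". The Abstract agrees.

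**Arms.** Section 2.5 allocates 48 participants to two groups of 24. There is no group without the EP.

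**Conclusion.** Section 4 names the whole combination, down to "online sessions of a telecare family-centered EP, which includes AOT activities, may be effective to improve participation".

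**Regular physiotherapy in the EG.** The Abstract and the opening of section 2.8.2 mention it only for controls. The telecare paragraph of section 2.8.1, under the experimental-group heading, describes the EP as "complementing their standard PT routines". The last sentence of section 2.8.2 speaks of all participants and of existing treatment being kept up.

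**The concern.** A randomised comparison informs on what differs between the arms. Here the aim and conclusion name three elements (GDT, TGT, and the EP with AOT), but the third is given equally to both groups. A positive result worded as in section 4 would credit the EP, AOT and telecare with a benefit that the comparison did not examine. A null result could be read as failure of the package when part of it may have helped both groups equally. The limitations paragraph of the Discussion does not mention this.

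The unclear status of regular physiotherapy in the EG adds a second uncertainty. The contrast is either the face-to-face programme in place of regular physiotherapy or on top of it, and these are different questions.

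**Working it through.** **1. Sessions and contact time.** Inputs are from section 2.8.1 and the Abstract.

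- The plan's total reproduces: 12 face-to-face + 6 online = 18 sessions, or 3 per week × 6 weeks. This takes the six online sessions as the programme total, one per week, as the telecare paragraph states.
- Face-to-face time at the stated 75 min: 12 × 75 = 900 min = 15 h. From the stated components, 50–60 + 15 = 65–75 min per session, so 12 × 65 = 780 min = 13 h up to 15 h.
- EP time: 6 × about 60 min = about 6 h in the EG and about 6 h in the CG. The difference is 0.
- Share of the experimental package with no difference in exposure: 6/18 = one third of sessions, or about 6 of 19 to 21 h.

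**2. What the comparison estimates.** Write EG and CG for the mean outcomes under the two assigned regimens, and R for the mean under regular physiotherapy without the EP, a condition that the trial does not contain. Then

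EG − R = (EG − CG) + (CG − R).

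- EG − CG is what the trial estimates: the face-to-face programme against, or added to, regular physiotherapy, with the EP in both arms.
- CG − R is the effect of adding the EP to regular physiotherapy. No arm supplies R, so it cannot be estimated.
- EG − R is the effect of the whole package over regular physiotherapy alone. It needs both terms.

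This identity needs no assumption of additive effects. Additivity is needed only for the stronger statement that the EP contributes nothing to EG − CG. If the EP changes how well the face-to-face training works, that interaction is inside EG − CG and cannot be separated out.

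**3. What each result would mean.** If EG − CG > 0, the package beats regular physiotherapy plus EP. If CG − R ≥ 0 (the EP does no harm), it also beats regular physiotherapy alone. If EG − CG is about 0, then EG − R is about CG − R, which is unknown.

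**4. Size, as an illustration only.** Section 2.3 plans 20 evaluable participants per group (40 in all; 40 × 1.2 = 48). It gives no effect size, SD or planned power, and the article states no alpha. Assume SD 1, two-sided alpha 0.05, and a whole-package effect EG − R of 0.8 SD. With n = 20 per group, power ≈ Φ(d√(n/2) − 1.96), and the difference detectable with 80% power is (1.960 + 0.842) × √(2/20) = 0.89 SD.

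| Share of the 0.8 SD due to adding the EP | Expected EG − CG (SD) | Power |
|---|---|---|
| 0% | 0.80 | 72% |
| 25% | 0.60 | 48% |
| 50% | 0.40 | 24% |
| 75% | 0.20 | 9% |
| 100% | 0 | no more than alpha |

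The larger the EP's share, the less likely the trial is to show a difference, although the package works equally well in every row.

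**5. Analysis.** Section 2.9 speaks only of the effectiveness of the intervention, by regression and repeated-measures models. Change within each arm has no control, so it cannot supply CG − R.

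**The case against.** The strongest reply is that the design is legitimate and openly stated. The full package is randomised against an active comparator, the Abstract describes that comparator soon after the aim, and the conclusion says only that the combination may be effective. No passage sets out to apportion benefit to AOT or telecare. This stands in large part: the comparison is valid, and nothing about the arms needs to change. It does not remove the mismatch, because the aim and conclusion still name the EP with AOT as part of what is shown to work, without saying that controls receive it too.

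A reader might go further and infer any of the following, none of which the documents support.

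- *The trial cannot show that the package works.* It can show superiority over regular physiotherapy plus EP and, if the EP is harmless, over regular physiotherapy alone.
- *The EP drops out, leaving a pure effect of GDT and TGT.* Exposure is balanced, but section 2.8.1 describes EP session 2 as helping carry what is learned in therapy into daily settings, so an interaction is plausible.
- *Every claim about family- or child-centred care must go.* The Discussion says "The findings of this study will help to highlight the importance of family/child/adolescent-centered interventions tailored to their specific needs". Part of that tailoring is in the EG-only sessions, where section 2.8.1 builds 45 min of functional training around each participant's interests and needs. Only what rests on the shared EP lacks a contrast.
- *The experimental group gives up regular physiotherapy.* The Abstract and the opening of section 2.8.2 could suggest it, but the telecare paragraph of 2.8.1 and the last sentence of 2.8.2 point the other way. That last sentence stands under the control-group heading, so it does not settle the matter. Figures 1 and 2 and the full protocol, which might, are not available here.

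That type and amount of therapy may differ together is common in comparisons with usual care and is no fault in itself. How regular physiotherapy is recorded is operational detail that an article may leave to the full protocol.

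**Conclusion.** The concern holds as a mismatch between the stated aim and conclusion and the contrast that is randomised. The trial estimates the effect of 12 face-to-face GDT and TGT sessions against, or added to, regular physiotherapy, given the same EP with AOT in both groups. It provides no evidence on the contribution of the EP, AOT or telecare, and a null result would not show that the package fails against regular physiotherapy alone.

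The fact that both arms receive the EP rests on explicit text in the Abstract and section 2.8.2 and on no assumption. The power figures rest on assumed values and only show the direction and possible size of the effect on a null result. The between-arm estimate itself is sound, so this is a fault of wording and interpretation of moderate weight, not a defect that invalidates the design. It is worth correcting because it governs what the main result may be said to mean.

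**What to change.** 1. Restate the aim (Abstract, Introduction) and the conclusion (Abstract, section 4) as the effect of 12 face-to-face GDT and TGT sessions compared with regular physiotherapy, with the same EP including AOT in both groups.
2. Make no efficacy claim for the EP, AOT or telecare component. Present any change within a group as uncontrolled description.
3. Reconcile the Abstract, section 2.8.1 (telecare paragraph) and section 2.8.2 on whether the experimental group keeps its regular physiotherapy, and state the contrast as replacement or addition accordingly.

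This changes wording only. It needs no change to arms, sample size, outcomes or analysis. The downside is a narrower claim.

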### 2.9. Statistical Analysis

First, a descriptive analysis of the study variables will be performed and, in the case of quantitative variables, the normality criteria will be checked. We will test whether there were differences after randomization between the two intervention groups. For this purpose, the appropriate bivariate tests will be used according to the type of variable. In a second stage, the effectiveness of the intervention will be analyzed, both in the short and medium term, adjusting for those variables that, according to previous analyses or due to the researchers’ consideration, could cause confusion. For these purposes, various logistic or linear regression models will be used (depending on the outcome variable). Finally, repeated measures models will be proposed in order to assess the evolution over time of the outcome variables.

The analysis will be performed both by protocol and by intention to treat.

The statistical package Statistical Package for the Social Sciences software (version 29, SPSS Inc., Chicago, IL, USA) or the statistical package STATA MP v18 (StataCop LLC, College Station, TX, USA) will be used.

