### 2.3. Sample Size Calculation

The authors have not found meta-analyses nor systematic reviews about the impact of the PT interventions for improving participation. The meta-analyses and systematic reviews consulted on different interventions for improving the functionality of children and adolescents with CP include samples from 10 to 30 participants [12,16,18,34,35,36]. Study samples from the CP population are not very large due to the variety of interventions and parameters for assessing function in PT interventions. As far as the authors know, there is no consensus on the parameter or predicted change in order to better estimate a sample size. Therefore, in this study, authors opted to obtain a larger sample than most previously published studies, considering 40 participants (20 in each group) for inclusion. Considering a 20% dropout rate, a total of 48 participants should be included—24 in the experimental group (EG) and 24 in the control group (CG). At the end of this study, the statistical power will be calculated.

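### Adjustment variables are to be chosen by baseline significance tests or open judgement, with no commitment to each outcome's own baseline score

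*Protocol article*

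**What the plan says.** Section 2.9 (Statistical Analysis) of the protocol article sets out a sequence.

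- **Step 1, group comparison.** "We will test whether there were differences after randomization between the two intervention groups", using bivariate tests suited to the type of variable.
- **Step 2, effectiveness.** Short- and medium-term effects are analysed "adjusting for those variables that, according to previous analyses or due to the researchers’ consideration, could cause confusion". For this, "various logistic or linear regression models will be used (depending on the outcome variable").
- **Step 3, time course.** "repeated measures models will be proposed in order to assess the evolution over time of the outcome variables".

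No covariates are listed and the baseline score is not named. Yet section 2.7 says that "sociodemographic, clinical, and outcome variables will be collected at baseline assessment", and Table 1 marks participation, gross motor function, gait, balance and functional goals at A0, A1 and A2.

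On size, section 2.3 describes "considering 40 participants (20 in each group) for inclusion" and continues: "Considering a 20% dropout rate, a total of 48 participants should be included". It gives no effect size, SD, correlation, significance level or target power.

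**The concern.** The article states a selection rule here, so this is more than detail left to an analysis plan. The rule has two routes, and each has a weakness.

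The first route is the baseline test. Under proper randomisation, any baseline difference is due to chance, so the test examines a null hypothesis already known to be true. Its p-value says nothing about how strongly a variable predicts the outcome, which is what makes a covariate worth including. A strongly prognostic baseline score will usually look balanced and be left out.

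The second route is the researchers' consideration, with no point in time by which the choice must be made. If covariates can be settled after the results are known, more than one adjusted answer is available for each outcome.

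Precision is at stake in a trial of about 40 evaluable participants spanning GMFCS levels I–III and ages 6 to 17, and so is control of the false-positive rate.

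**Working it through.** **Inputs from the documents.** 20 evaluable per group; 48 randomised 1:1; outcomes measured at A0, A1 and A2 (sections 2.3, 2.5, 2.7 and Table 1). The plan's own total reproduces as 40 × 1.20 = 48. (Dividing instead, 40 / 0.80 = 50; and 48 × 0.80 = 38.4, so 20 per group is slightly generous.) The 40 comes from no power formula, so there is no stated power to reproduce.

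**Assumptions, not in the documents.** Two-sided alpha 0.05; true difference d = 0.5 SD; correlation ρ between A0 and the follow-up score of 0.5 to 0.8, with 0.9 as an extreme; normally distributed scores; a 5% threshold for the baseline test.

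**Step 1: gain from always adjusting.** Adjusting for A0 multiplies the residual variance by 1 − ρ². By the normal approximation,

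power = Φ( d / [√(1 − ρ²) × √(2/20)] − 1.96 ).

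- No adjustment: 0.5 / √0.1 = 1.58; Φ(−0.38) = 35%.
- ρ = 0.5 (factor 0.75): 1.83; Φ(−0.13) = 45%.
- ρ = 0.7 (factor 0.51): 2.21; Φ(0.25) = 60%.
- ρ = 0.8 (factor 0.36): 2.64; Φ(0.68) = 75%.

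The difference detectable with 80% power is 2.80 × √(1 − ρ²) × √0.1. That is 0.89 SD unadjusted, against 0.77, 0.63 and 0.53 SD at these three correlations.

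**Step 2: the routes compared by simulation.** 20,000 trials per setting, 20 per group, t-based tests. Test-then-adjust uses the A0 score only if the baseline t-test has p < 0.05, which happens in about 5% of trials.

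| ρ | Power, unadjusted | Power, test-then-adjust | Power, always adjust | Type I error, test-then-adjust | Type I error, better of adjusted and unadjusted |
|---|---|---|---|---|---|
| 0.5 | 34% | 34% | 42% | 4.4% | 7.4% |
| 0.7 | 34% | 34% | 56% | 3.6% | 8.1% |
| 0.8 | 34% | 35% | 72% | 3.0% | 8.6% |

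The simulated powers are a little below those of step 1 because they use the t distribution. Repeat runs for always adjusting at ρ = 0.5 gave 41–42%. This is why ranges such as 41–45% are quoted.

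**Step 3: reading the table.** The test-driven route behaves almost like no adjustment. It is conservative: it loses power and does not create false positives. The judgement route can err the other way. The last column assumes that the smaller of the two p-values is reported, which is the worst use of a choice between just these two analyses.

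**Step 4: what a repeated measures contrast would recover.** If A0 is one of the time points, the change contrast has variance 2(1 − ρ) in place of 1. At ρ = 0.5 that equals 1, so nothing is gained. At ρ = 0.7, 0.8 and 0.9 it equals 0.6, 0.4 and 0.2, and simulated power is about 51%, 68% and 93%. Always adjusting gives 56%, 72% and about 93–94%.

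**The case against.** The strongest reply is that section 2.9 does not forbid the right analysis. It sets no p-value threshold and joins its two routes with an or, so the researchers may simply decide always to adjust for A0. It also lists repeated measures models, which, if they include A0, would recover much of the loss at correlations of 0.7 and above. The phrase about earlier analyses most naturally means the baseline tests just described, but it is slightly ambiguous. All of this stands, and it makes the power loss conditional.

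A reader might infer that the plan wastes about half its power. The documents do not support that as a general statement, since they give neither a correlation nor an effect size. By the step 1 formula, the share of adjusted power lost without adjustment at d = 0.5 is 21%, 41%, 53% and 63% for ρ of 0.5, 0.7, 0.8 and 0.9. About half is the loss of information (residual variance) near ρ = 0.7, which is a different quantity.

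A reader might also fault the mention of logistic regression, since every named outcome is a score or measurement. The wording is generic, and sections 2.7 and 2.9 do not rule out a responder analysis: section 2.7 gives minimum important differences for the gross motor and balance scales. Which model decides, and the exact repeated measures specification, may properly sit in an analysis plan that is not shown. Neither is pressed here.

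The reply does not remove the stated rule. A plan that names baseline tests and open judgement as its selectors, and no fixed covariate, leaves the choice open until the data are in hand.

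**Conclusion.** The point holds in a limited form. Section 2.9 lets baseline significance tests or undated judgement select the adjustment variables, and it does not commit to the A0 score that the trial collects for every outcome.

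If the tests decide, power for an assumed 0.5 SD effect stays near 34%, when prespecified adjustment would give about 41–45%, 56–60% and 72–75% at correlations of 0.5, 0.7 and 0.8. If post-hoc judgement decides, type I error can rise from 5% to about 7–9% over the same correlations.

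These sizes rest on the assumed effect, correlations, alpha and test threshold, and on 20 evaluable per group. They show what the open rule can cost, not what it must cost. The case for prespecifying the A0 score does not depend on any one of these values.

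**What to change.** Amend section 2.9, or the analysis plan that governs it, before outcome data are seen:

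1. Keep the descriptive baseline table by group, but drop significance tests of baseline differences as a way to choose covariates.
2. State that the A1 and A2 group contrasts, for every outcome with a baseline value, are adjusted for that outcome's own A0 score. One linear mixed model giving both contrasts, or an ANCOVA at each visit, would serve; other valid parameterisations that use A0 are acceptable if fixed in advance.
3. Name any further covariates now, for example GMFCS level and age.
4. Label every other covariate set as a sensitivity analysis.

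The cost is wording and one or a few degrees of freedom per model: with 40 evaluable, the A0 score takes the residual degrees of freedom from 38 to 37. No new data, visits or participants are needed, because the A0 scores are already scheduled and GMFCS level and age are needed for eligibility.
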